## Sample Size Calculation

Sample size was calculated using the primary outcome of accessibility in WINPEPI® (PEPI-for-Windows) version 11.65. For this two-sided ( $\alpha = 0.05$ ) superiority analysis, these computations were made based on a t-test with the null hypothesis that there is no difference between the WHO eTB and WHO TB in the accessibility of information.

$H_0$ : WHO eTB = WHO TB

$H_1$ : WHO eTB  $\neq$  WHO TB

With sample sizes of 122 per arm (244 total) we would achieve 80% power to detect a difference on the Likert-scale of 0.5 (effect size) with a standard deviation of 1.0 between intervention and control groups. We applied the effect size and standard deviation from previous studies on GRADE SoF tables. We assumed that 15% of those starting would not complete the survey, but we did not factor stratifying participants by stakeholder group into the calculation, as the aim of stratification was to balance participants rather than be sufficiently powered to detect subgroup effects.

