### Randomization

Participant response to a question on their role as a participant in this study will be used for stratification into one of four categories described in Figure 1. Participants within each of these categories will be randomly assigned in a 1:1 ratio to the WHO eTB or WHO TB arms.

Participants will also be randomly assigned to access one of two recommendations in a 1:1 ratio. The same two recommendations will be presented for both arms and selected because they contain mostly plain language and were more accessible to non-clinical participants.

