### Inferential Analysis

We will perform a primary analysis including all randomised participants, except for those who completed the survey in less than five minutes. We determined this cut-off a priori because user testing determined that it would be impossible to complete the work in that time. We will conduct a second per-protocol analysis which excludes participants who were flagged by SurveyMonkey® software (see below). For the outcomes of accessibility and satisfaction, we will use t-tests and mean differences 95% confidence intervals (95% CIs) to compare means and standard deviations (SDs) between the intervention and control groups. For the outcome of understanding, we will use  $\chi^2$  tests and risk difference (RD) with 95% CIs to compare the proportion of correct responses between groups. Finally, for preference, we will present preference as mean (SD) overall and for both trial arms. Skewness, Shapiro-Wilk tests, and histograms will be used to evaluate whether the distribution was shifted toward the same preference in both groups. Levene's test of equal variances will be used for all t-tests and degrees of freedom were adjusted for  $p < 0.05$ . We will report all p-values to three decimal places, with values less than 0.001 reported as  $< 0.001$ .

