### Dropouts, missing data, and poor-quality responses

We will use available case analysis for data from participants who responded to some survey questions after being assigned to the intervention. In order to prevent dropouts and missing data, we plan to implement the following strategies: (1) disseminating short emails to target stakeholder groups with a direct link to the survey, (2) informing participants that the survey will require 15 minutes, (3) participants who complete the survey have the option to enter a draw for a gift card, (4) all outcome questions are marked as mandatory, and (5) participants are randomised only after the collection of baseline characteristics.

We define participants who spend less than five minutes on the survey as inappropriate in our analyses, with the rationale that practical comprehension and completion of the survey could not be performed in five minutes. The average survey completion time is estimated to be 15 minutes. This is anticipated to prevent analysis of erroneous responses from participants who sought to simply gain access to the content of the survey or enter the gift card draw. For the per-protocol analysis, we will use a pre-defined but unknown SurveyMonkey® algorithm which flags poor-quality responses for straight-lining. Straight-lining is defined by SurveyMonkey® as responses to questions with the same answer option or pattern. Participants flagged for straight-lining, as well as those who spend less than five minutes on the survey, will be removed from the per-protocol analysis.

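### A Levene pre-test chooses the t-test for the primary outcome; using Welch throughout would remove a small, avoidable dependence at almost no cost

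*Protocol*

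**What the plan says.** Under Inferential Analysis, accessibility and satisfaction are compared by t-tests with mean differences and 95% confidence intervals. The same paragraph adds: "Levene's test of equal variances will be used for all t-tests and degrees of freedom were adjusted for" Levene p < 0.05. I read this as the usual two-row SPSS output: the equal-variance row is reported unless Levene's test is significant, and otherwise the unequal-variance (Welch) row. The rule covers all t-tests, so it includes the primary accessibility composite.

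Sample Size Calculation sets the frame: "For this two-sided ( $\alpha = 0.05$ ) superiority analysis", with "With sample sizes of 122 per arm (244 total) we would achieve 80% power" for "a difference on the Likert-scale of 0.5 (effect size) with a standard deviation of 1.0". On losses it states: "We assumed that 15% of those starting would not complete the survey".

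Four statements bear on the sizes of the analysed arms:
- Randomization: "Participants within each of these categories will be randomly assigned in a 1:1 ratio".
- Allocation Concealment: the sequence comes from a commercial SurveyMonkey algorithm whose workings are unknown.
- Inferential Analysis: anyone finishing in under five minutes is left out of the primary analysis.
- The section on dropouts and missing data keeps partial responders wherever they answered: "We will use available case analysis for data from participants who responded to some survey questions after being assigned to the intervention". The same section makes all outcome questions mandatory and places randomisation after the baseline questions.

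**The concern.** Levene's test has limited power against modest differences in spread, so a non-significant result does not show that the pooled standard error is right. When the arms are of equal size, the pooled and Welch standard errors coincide and the choice hardly matters. When the smaller arm has the larger SD, the pooled standard error is too small and the test is liberal. When the larger arm has the larger SD, it is too large and the test is conservative.

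Time on task and completion could depend on the platform, so the exclusions and break-offs may differ between arms. What is at stake is whether the two-sided 0.05 level and the 95% intervals hold as stated, when their standard error is picked by a preliminary test on the same data.

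**Working it through.** **Inputs from the protocol.** Two-sided alpha 0.05, 122 per arm, SD 1.0, 1:1 allocation, 15% non-completion, Levene threshold 0.05.

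**Inputs assumed.** The protocol gives no arm-specific SDs and no arm-specific losses. I take SD ratios from 1.0 to 1.5 and show a range of arm sizes.

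**The plan's own figure.** For 80% power, n = 2(1.960 + 0.842)² × 1.0² / 0.5² = 62.8, so 63 per arm (64 with the exact t), or 63/0.85, about 75, after 15% loss. The stated 122 per arm is not reproduced; it gives about 97% power. That is a separate matter, and here 122 serves only as the planned arm size.

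**Arm sizes to expect.** With 15% loss in each arm, 122 × 0.85 = 103.7, so about 104. Simple 1:1 randomisation of 244 would give 122 ± 1.96 × √(244 × 0.25) = 122 ± 15.3, or about 107 to 137. Taking 15% from 137 and 107 leaves about 116 and 91, close to the 116/92 case below.

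**Why imbalance matters.**
- Pooled: SE² = s_p²(1/n₁ + 1/n₂), with s_p² = [(n₁−1)s₁² + (n₂−1)s₂²]/(n₁+n₂−2).
- Welch: SE² = s₁²/n₁ + s₂²/n₂.

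For 116/92 with SDs 0.9/1.1:
- s_p² = (115 × 0.81 + 91 × 1.21)/206 = 0.987.
- Pooled SE = √(0.987 × 0.01949) = 0.1387. Welch SE = √(0.00698 + 0.01315) = 0.1419. The ratio is 0.977.
- Always pooling would give about 2[1 − Φ(1.96 × 0.977)] = 5.5%.

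For 110/60 with the same SDs:
- s_p² = (109 × 0.81 + 59 × 1.21)/168 = 0.950.
- Pooled SE = 0.1565, Welch SE = 0.1659, ratio 0.943. Always pooling would give about 6.5%.

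The two-stage rule falls between always pooling and Welch.

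**How often the pooled test is kept when SDs truly differ** (simulated, arms from 122/122 to 163/81):
- SD ratio 1.1: 84–86%
- SD ratio 1.2: 53–65%
- SD ratio 1.3: 24–37%
- SD ratio 1.5: 2–6%

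**Simulated type I error** (normal data, mean-centred Levene, 40,000–60,000 replicates, Monte Carlo SE about 0.1 point):

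| Analysed arms | Loss from 122 each | SDs | Two-stage | Welch | Gap (points) |
|---|---|---|---|---|---|
| 104/104 | 15% / 15% | 0.9/1.1 | 5.0% | 5.0% | 0 |
| 110/98 | 10% / 20% | 0.92/1.08 | 5.04% | 4.94% | 0.1 |
| 116/92 | 5% / 25% | 0.9/1.1 | 5.16% | 4.94% | 0.2 |
| 122/91 | 0% / 25% | 1.0/1.2 | 5.3% | 4.9% | 0.4 |
| 110/73 | 10% / 40% | 0.92/1.08 | 5.3% | 4.9% | 0.4 |
| 110/60 | 10% / 51% | 0.9/1.1 | 5.8% | 5.1% | 0.7 |
| 163/81 | stress case | 1.0/1.2 | 5.50% | 4.91% | 0.6 |
| 163/81 | stress case | 1.2/1.0 | 4.44% | 4.95% | −0.5 |

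In the 110/98 and 116/92 rows the two procedures reached different decisions in 0.10% and 0.22% of data sets, about 1 to 2 per 1,000.

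**Coverage.** Levene's test is unaffected by a shift in means, so with normal data the 95% interval's coverage is 100% minus the type I error above, whatever the true difference. For 163/81 with SDs 1.0/1.2, coverage is 94.5% for the two-stage rule and 95.1% for Welch.

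**Power cost of Welch with equal SDs.** At 122/122 and a difference of 0.5, both give 97.3%. At 122/80, Welch gives 93.1% against 93.2%. At 122/80 with a difference of 0.36, it gives 69.8% against 69.9%.

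**The case against.** The strongest reply is that the rule is prespecified, deterministic and matches what SPSS prints; it contradicts nothing and leaves no discretion. The planned design is also close to the case where it is harmless: 1:1 allocation, 15% loss overall, mandatory outcome questions that largely confine missing items to people who break off, and randomisation only after baseline. Where the variances differ strongly, Levene's test usually switches to Welch anyway. If one arm really lost 40–50%, attrition bias would outweigh half a point of alpha, and Welch would not cure it.

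All of that stands, and it fixes the size of the point. It does not make the two-stage rule the better choice, since Welch does at least as well on error rates in the cases checked and costs almost nothing.

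A reader might infer something stronger: that an easier eTB platform would keep more participants and bunch their ratings at the top of the scale, so the larger arm has the smaller variance and false positives are inflated. The protocol does not support this. If eTB is truly easier, the null hypothesis is false and there is no false positive to inflate; only interval coverage is affected. Bunching at the top also means bounded, non-normal scores. In simulations of a bounded 7-point composite (scale length and means assumed), the coverage gap was only about 0 to 0.3 points.

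**Conclusion.** The point holds as a minor, free improvement. The protocol makes the standard error of its primary comparison depend on a preliminary test. This is harmless with equal analysed arms, and equal arms are planned but not guaranteed.

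At an assumed SD ratio near 1.2, the type I error and coverage differ from Welch's by about 0 to 0.2 points when losses average the stated 15% and split no further than 5% against 25%. The gap reaches about 0.3 to 0.7 points only when loss is markedly one-sided, and the direction reverses if the larger arm has the larger SD. Figures of 5.5–5.8% should not be read as forecasts for this trial, because nothing in the protocol points to losses of 40–50% in one arm.

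These results rest on assumed SDs and arm sizes and on normal data. A changed conclusion would be rare.

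**What to change.** Replace the Levene sentence under Inferential Analysis with: 'Welch's t-test and its 95% CI will be used for all accessibility and satisfaction comparisons; no preliminary test of equal variances will be used to choose the test.'

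The cost is one sentence. SPSS already prints the unequal-variance row, so no new software or data are needed. The change fixes one standard error and one interval per comparison in advance, in both the primary and the per-protocol analysis.

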### Dropouts, missing data, and poor-quality responses

We will use available case analysis for data from participants who responded to some survey questions after being assigned to the intervention. In order to prevent dropouts and missing data, we plan to implement the following strategies: (1) disseminating short emails to target stakeholder groups with a direct link to the survey, (2) informing participants that the survey will require 15 minutes, (3) participants who complete the survey have the option to enter a draw for a gift card, (4) all outcome questions are marked as mandatory, and (5) participants are randomised only after the collection of baseline characteristics.

We define participants who spend less than five minutes on the survey as inappropriate in our analyses, with the rationale that practical comprehension and completion of the survey could not be performed in five minutes. The average survey completion time is estimated to be 15 minutes. This is anticipated to prevent analysis of erroneous responses from participants who sought to simply gain access to the content of the survey or enter the gift card draw. For the per-protocol analysis, we will use a pre-defined but unknown SurveyMonkey® algorithm which flags poor-quality responses for straight-lining. Straight-lining is defined by SurveyMonkey® as responses to questions with the same answer option or pattern. Participants flagged for straight-lining, as well as those who spend less than five minutes on the survey, will be removed from the per-protocol analysis.

## Interim Analysis

We will perform pre-planned interim analysis based on the thesis defence date of the first author (MM). The interim analysis will not be used to stop the study or draw final conclusions.

## Discussion

### Research in Context

To our knowledge, this is the first RCT comparing stakeholder feedback on the presentation of two guideline platforms. Nevertheless, several studies have explored stakeholder perceptions of guideline development and presentation, as well as the factors that influence their uptake. One qualitative study by Fearn, et al. explored public perceptions of clinical practice guidelines and found that participants desired information to help them make decisions, but current numerical formats may not always be accessible to a public audience. Additionally, a content analysis by Santesso, et al. found that patient versions of guidelines may not always address stakeholder needs, as they rarely include important EtD information, such as beliefs, values and preferences, accessibility, costs and feasibility. Furthermore, a realist review by Kastner, et al. which sought to identify the factors associated with guideline uptake, found that effective communication of content, including simple, clear and persuasive language, improved the implementability of guidelines by stakeholders.

This trial will expand on the methods of previous RCTs used to evaluate the presentation of guideline information, specifically, comparing new GRADE SoF tables to conventional formats. These studies evaluated participant understanding, accessibility, satisfaction and preference. Carrasco-Labra, et al. and Vandvik, et al. identified that stakeholders preferred the presentation of risk differences over absolute risk estimates, as well as the inclusion of narrative statements to supplement numerical data. Furthermore, Akl, et al. found that participants demonstrated a better understanding of strength of recommendations and quality of evidence when this information was presented as symbols, rather than numbers. Similar to our trial, these studies objectively evaluate perceptions of new to conventional formats to identify areas of improvement.

### Strengths and Limitations

This study is anticipated to have several strengths. First, we use a randomised design conducted and reported in accordance with the CONSORT statement on randomised trials, which reduces the risk of confounding, selection and reporting bias. Second, we use several previously validated outcomes from similar trials. Third, we gather feedback from diverse group of stakeholders, thus improving the generalizability of findings using a carefully developed approach to presenting recommendations.

This study also has some limitations. First, the ability to blind participants is limited, as some may have been aware of eTB development. We consider this probability to be small, as the main publication and awareness campaigns will begin after the majority of participants have been recruited. Second, data will be collected using an online survey and, thus, there is limited control over the environment in which the survey is performed. Third, participants may claim to

be part of more than one stakeholder group (e.g. a healthcare provider involved in research), but they are required to select just one for stratification. Fourth, we did not power our trial to conclusively evaluate results by participant strata.

### Implications for Policy and Practice

Tuberculosis guideline recommendations developed by the WHO assist stakeholders in making evidence-informed decisions on TB prevention, diagnosis, treatment, and care. According to the Guidelines International Network (G-I-N) and the National Institute for Health and Care Excellence (NICE), stakeholder engagement is important to ensuring that guideline products are feasible and acceptable to end-users. This study will engage stakeholders in evaluating the presentation of recommendations through the outcomes of accessibility, understanding, and satisfaction, which are surrogates for the correct implementation of evidence in practice.

### Implications for Research

This study is anticipated to demonstrate how RCTs may be used to compare stakeholder feedback on guideline platforms. Future studies should seek to explain the findings of this trial through qualitative and user testing techniques, such as the study by Rosenbaum, et al. for SoF tables. Furthermore, additional trials should focus on specific stakeholder groups, such as patients and the public, to determine optimal ways to present recommendations.

